#### Reporting Baseline and Demographic Characteristics

To describe participant characteristics, authors of member studies include a table containing descriptive statistics, given as n (%) for categorical variables, and mean (SD) or median (25th-75th percentile) for continuous variables. A column containing *P* values will not be included, as statistical tests do not meaningfully assess differences between samples or populations, nor should they be used as the basis for assessing confounders [28].

#### Estimating Risk Ratios, Odds Ratios, and Hazards Ratios

Each study is required to use risk ratios (estimated by Poisson regression with robust SE) as the primary means of assessing the association of dietary intake with CMDs. Risk ratios are based on incident cases, and so models will need to exclude participants with depression or anxiety at baseline. Furthermore, to determine incident risk, studies must have dietary exposures at baseline and depression, or anxiety measured at a subsequent time point. Where the estimation of a risk ratio is not possible (refer to Figure 2), for example, where the total number of people exposed at baseline is not available (such as for retrospective or case-control studies) [29], odds ratios are estimated using standard logistic regression techniques. Where only time-to-event data are available, hazard ratios are used, estimated by a Cox proportional hazards model. For rigor, all effect estimates will be accompanied by a 95% CI and exact *P* value [30].

Models can be fitted using any statistical analysis software, including R (R Core Team), SAS/STAT (SAS Institute Inc), Stata (StataCorp LLC), and SPSS (IBM Corp). Before fitting the relevant models, Member studies must assess model assumptions. Should any model assumptions be violated, an alternate approach to analysis may be selected. For example, the nonlinearity of continuous variables should be investigated, and transformations or nonlinear models fitted where necessary. Similarly, should any of the assumptions of Cox proportional hazards models be violated, alternative strategies will be deployed to account for these violations.

In addition to the models listed above, the following subgroups shall be fitted separately for each exposure-outcome pairing, where data allows: (1) sex, (2) age, (3) year (for longitudinal studies with multiple waves of follow-up), (4) country (for multicenter studies), and (5) all symptom scales and diagnostic measures (for studies with depression and anxiety measured via multiple measures. For age, studies should explore the relationship between the risk factors and mental disorders with age to see if a continuous measure is appropriate. Where a continuous measure is not appropriate, studies should generate appropriate age categories for their dataset by inspecting the frequency of outcomes by age groups. As a guide, the GBD currently uses 0-6 days (early neonatal), 7-27 days (late neonatal), 28-365 days, 1-4 years, 5-9 years, then 5-year intervals from 10-95 [31].

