#### Covariates and Confounders

To address the anticipated heterogeneity of member studies’ available data, a set of core confounders are provided for the purpose of generating a consistent minimally adjusted analysis. The conduct of additional analyses (eg, using additional variables, fitting sensitivity models, or exploratory analyses) is at the discretion of the study author or authors based on available data and reviewer requests when studies are submitted for publication.

To be included in the GLAD project, member studies must adhere to the iteratively adjusted models (Textbox 1).

The iteratively adjusted statistical models required for the Global burden of disease Lifestyle And mental Disorders (GLAD) task force.Model 1: Unadjusted model, with the dietary variable (as listed in Table 2) as the exposure and depression or anxiety as the outcome.Model 2: Minimally adjusted model, with the dietary variable of interest, depression or anxiety, and with baseline mental disorder status (or lifetime history of mental disorders for cross-sectional studies), age, sex, and a measure of socioeconomic status, such as household income, employment status, or education.Sensitivity model: Same as model 2, but with adjustment for total energy intake.

Of particular relevance in nutritional epidemiology are methods for adjusting for energy intake. Intake of specific nutrients are correlated with total energy intake, and so appropriate adjustment is required to disentangle the effect of the nutrient from the effect of energy. For example, an individual may alter intake of a specific nutrient by changing dietary composition, and not by changing total energy intake. As such, controlling energy intake can reduce confounding, and failure to appropriately control for total energy intake may nullify associations between nutrient intake and disease outcomes [27]. Given the correlation between nutrient intake and energy, the application of Willett’s residual method is recommended to account for total energy intake [27]. This involves fitting a regression model with the dietary variable as the outcome and total energy intake as the exposure, predicting residuals from this model, and then using these predicted residuals in the analysis models [27].

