#### Missing Data

Each study initially uses a complete-case model, whereby individuals with missing observations are excluded from the model. Member Studies with missing exposure, outcome, and covariate observations conduct a missing data analysis to determine the influence of missing data. While a multiple imputation approach is preferred, other methods such as k-nearest neighbor imputation or inverse probability weighting may be used where an imputation approach is not possible or appropriate [36-41].

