## Results

As of August 2024, 18 longitudinal studies have agreed to participate in the GLAD project (Table 3). These studies have sample sizes ranging from 639 participants to 171,000 participants (Table 4).

The GLAD project comprises 3 essential phases, which will be repeated for other lifestyle exposures of interest: (1) conducting a systematic search to identify relevant studies and recruit study leads to contribute data, (2) generating estimates of study-level associations of dietary risk factors with CMDs using harmonized data analysis protocols developed by the GLAD Taskforce and approved by the GBD, and (3) pooling results from each study to provide the GBD with robust estimates to calculate the diet-CMD risk-outcome pairs in the first instance.

As of August 2024, phase 1 of the GLAD project has been completed, and phase 2 is due for completion in early 2025, at which time phase 3 of the GLAD project is due to begin (Figure 3).

Phase 1 includes searching for and recruiting studies with suitable data, harmonizing data definitions by ensuring member studies use the exposure definitions listed in Table 1 and the outcome definitions listed in Table 2, and harmonizing data analyses by ensuring member studies follow the statistical analysis plan presented in this paper.

**Table 3 table3:** Details of the ethics approval for currently listed member studies^a^.

Study name	Ethics review board
The African-PREDICT^b^ study [44]	North West Department of Health and Health Research Ethics Committee of the North-West University.
Child to Adult Transition Study [45]	Royal Children’s Hospital Human Research Ethics Committee.
Dunedin Study [46]	Health and Disability Ethics Committee, Ministry of Health.
Environmental Risk (E-Risk) Longitudinal Twin Study [47,48]	Joint South London and Maudsley and the Institute of Psychiatry Research Ethics Committee.
Fragility in the Elderly Lombardy Study [49]	Ethics committee of the University of Pavia.
Geelong Osteoporosis Study [50]	Barwon Health Human Research Ethics Committee.
Health4Life [51,52]	University of Sydney, NSW^c^ Department of Education, University of Queensland, Curtin University, and relevant Catholic school ethics committees.
Healthy Life in an Urban Setting [53]	Ethical Review Board of the Academic Medical Center Amsterdam.
Longitudinal Aging Study Amsterdam [54]	Medical ethics committee of the VU University Medical Center.

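### Cohorts that hold event or censoring dates are steered to a primary risk ratio that ignores unequal follow-up

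*Protocol article*

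**What the plan says.** The rule is in the protocol article under Estimating Risk Ratios, Odds Ratios, and Hazards Ratios. It opens with "Each study is required to use risk ratios (estimated by Poisson regression with robust SE) as the primary means" of assessing diet against common mental disorders. Odds ratios are for designs in which a risk ratio cannot be estimated. Hazard ratios come last: "Where only time-to-event data are available, hazard ratios are used, estimated by a Cox proportional hazards model". On timing, the outcome need only be "depression, or anxiety measured at a subsequent time point". No offset, common horizon or length of follow-up is given.

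Other provisions bear on the point:

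- The same section adds: "Should any model assumptions be violated, an alternate approach to analysis may be selected". Its examples are nonlinearity and violated Cox assumptions.
- It also asks for separate fits by year in multi-wave studies, as a subgroup analysis where data allow.
- Covariates and Confounders says: "The conduct of additional analyses (eg, using additional variables, fitting sensitivity models, or exploratory analyses) is at the discretion of the study author".
- Missing Data says: "Each study initially uses a complete-case model, whereby individuals with missing observations are excluded from the model". A missing-data analysis follows, with multiple imputation preferred and inverse probability weighting among the alternatives.
- Future Directions: Meta-Analyses plans random-effects pooling, meta-regression on demographic factors and methodological biases, and cross-walking or sensitivity analyses, all under a separate protocol. Follow-up length is not named.

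All 18 listed member studies are longitudinal (Results). Medical records are named as an outcome source under Exposure and Outcome Definitions, and prescription codes in the notes to Table 2.

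**The concern.** A dated event can be reduced to a yes/no status. A cohort holding both status and dates therefore does not have only time-to-event data, and on the wording of the rule its primary estimate is the plain Poisson risk ratio. Where individual follow-up varies, through staggered entry, dropout or a register closing date, a participant observed for one year without an event then counts the same as one observed for ten.

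Two things are at stake. The first is bias within a study: if diet is related to how long people are observed, observation time is mixed into the diet effect. The second is comparability between studies: a cumulative risk ratio depends on the horizon, so a single underlying hazard ratio gives different risk ratios in short and long cohorts. The project's stated aim is robust, comparable evidence for the GBD, so both matter.

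**Working it through.** The document gives no follow-up length, retention or incidence, so there is no figure of the plan's own to reproduce. Every rate below is an assumption, and hazards are taken as constant.

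**1. Follow-up related to a continuous exposure, no true effect.** Assume an event rate λ = 0.02 per year and exponential follow-up with mean 5·exp(k·x) years, capped at 12 years, where x is diet in SD units. People censored without an event are coded 0. In simulation (n = 60,000, 20 runs each), k = 0.05, 0.10 and 0.20 (roughly 5%, 10% and 20% longer follow-up per SD) gave risk ratios without an offset of about **1.04, 1.08 and 1.15**. With a log(person-time) offset they were 1.00 to within simulation error of about 0.01.

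A closed-form check at x = 0:

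- The loss rate is c = 1/5 = 0.20, so λ + c = 0.22.
- The observed risk is (0.02/0.22)·(1 − e^(−0.22·12)) = 0.0909·0.9286 = 0.084.
- The slope of log risk in c is −1/0.22 + 12·0.0714/0.9286 = −3.62.
- Since dc/dx = −0.20k, the slope per SD is 0.725k.
- The ratios are exp(0.036) = 1.04, exp(0.072) = 1.08 and exp(0.145) = 1.16, in line with the simulation.

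**2. Two exposure groups, T = 10 years, λ = 0.02 in the unexposed.** With annual loss c, the observed risk is λ/(λ+c)·(1 − e^(−(λ+c)T)), and those lost are again counted as non-cases.

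| Annual loss, unexposed / exposed | Ratio if HR = 1.00 | Ratio if HR = 1.25 (full-follow-up RR 1.22) |
|---|---|---|
| 10% / 10% | 1.00 | 1.225 |
| 5% / 8% | 0.88 | 1.08 |
| 5% / 10% | 0.81 | 0.99 |
| 3% / 10% | 0.74 | 0.91 |

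For the 5% / 10% row under the null: 0.1165/0.1438 = 0.81. The person-time rate ratio is 1.00 or 1.25 in every row, provided censoring is independent of the outcome given exposure. Equal loss, even at 10% per year, produces essentially no bias.

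**3. One fixed wave, complete cases.** Take HR 1.25, λ = 0.02 and T = 10, so the risks are 0.2212 (exposed) and 0.1813 (unexposed).

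- If loss depends on exposure only, the risk ratio stays at 0.2212/0.1813 = **1.22**, with no bias.
- If loss depends jointly on exposure and outcome, with retention of non-cases/cases of 0.8/0.7 in the unexposed and 0.7/0.5 in the exposed, the observed risks are 0.1106/(0.1106 + 0.5452) = 0.169 and 0.1269/(0.1269 + 0.6550) = 0.162. The ratio is then **1.04**. This is informative dropout, which an offset does not by itself remove.

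**4. Horizon, with complete follow-up.** RR(T) = (1 − e^(−λ·HR·T))/(1 − e^(−λT)).

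| HR | Rate per year | RR at 1 year | RR at 10 years | RR at 20 years |
|---|---|---|---|---|
| 1.25 | 2% | 1.247 | 1.220 | 1.193 |
| 1.25 | 4% | 1.244 | 1.193 | 1.148 |
| 1.50 | 4% | 1.485 | 1.369 | 1.269 |

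In terms of reference cumulative incidence p, HR 1.50 gives RR = [1 − (1 − p)^1.5]/p: 1.49 at 3%, 1.46 at 10%, 1.38 at 30% and 1.34 at 40%. The gap is small when few people become cases.

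**The case against.** The strongest reply is that the plan does not tell anyone to code lost participants as non-cases. It starts from complete cases and follows with imputation or weighting. At a fixed wave, someone lost earlier has a missing outcome and is excluded, and step 3 shows no bias there if loss depends on exposure only. That stands for wave designs, including those that rely on symptom scales, where onset dates may be unknown anyway. It does not reach record or register follow-up that ends early: the outcome is an observed 0, so nothing is flagged as missing.

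A second reply is that the Cox sentence may be meant for any cohort with censored outcomes, and that Figure 2, which bears on the choice of ratio, is not shown. The wording is indeed ambiguous for cohorts holding both kinds of data. As written, though, it points them to the risk ratio. An offset is not forbidden, and supplementary hazard ratios are allowed, but only at the authors' discretion.

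Third, the by-year fits, the alternate-approach clause and the planned cross-walking offer some protection. It is partial: the fits are subgroups, unequal follow-up is not named as a trigger, and pooling cannot adjust for horizon unless studies report it. Dependence on horizon is also a property of a risk ratio, not an error in itself.

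A reader might go further and infer that every cohort with unequal follow-up will give a biased ratio, or that healthful foods will look falsely harmful. The documents support neither. Equal loss leaves the ratio essentially intact, and nothing in them says whether, or in which direction, retention is related to diet.

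**Conclusion.** The point holds in a limited form. The stated order of measures puts a model without follow-up time first even where dates exist, and no other provision names follow-up length. The primary estimate may be biased in cohorts where three conditions meet: individual follow-up differs, its length is related to diet, and early-censored people count as non-cases. Under the assumed rates the size is 1.04 to 1.15 per SD, or 0.74 to 0.88 between two groups when the exposed are lost faster, where the truth is 1.00. How many member studies meet these conditions cannot be told from the document.

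The lack of a common horizon needs no assumption about retention, but it is minor at low incidence and becomes material only with long follow-up or common outcomes. The rule should be changed before the study-level results are pooled. Systematic bias across the project is not shown.

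**What to change.** Change the trigger in Estimating Risk Ratios, Odds Ratios, and Hazards Ratios as follows:

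- Where follow-up differs between participants and event or last-contact dates exist, the primary estimate is Poisson regression with robust SE and a log(person-time) offset, or a Cox model.
- Where everyone analysed has the same fixed interval between waves, keep Poisson without an offset. The missing-data analysis remains the check on informative dropout.
- Every study reports follow-up length, events and person-years with each ratio, so that the planned meta-regression can account for horizon.

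The cost is one changed rule and, for cohorts that already hold dates, one changed model; the offset version keeps the same software and robust SE. The drawback is that some cohorts will report rate or hazard ratios instead of risk ratios, which the pooling must label and handle. The plan already admits risk, odds and hazard ratios, so this extends an existing task.

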Fruits	Average daily consumption of less than 310-340 g of fruit including fresh, frozen, cooked, canned, or dried fruit, excluding fruit juices and salted or pickled fruits.	grams/day
Vegetables	Average daily consumption of less than 280-320 g of vegetables, including fresh, frozen, cooked, canned, or dried vegetables and excluding legumes and salted or pickled vegetables, juices, nuts and seeds, and starchy vegetables such as potatoes or corn.	grams/day
Legumes	Average daily consumption of less than 90-100 g of legumes and pulses, including fresh, frozen, cooked, canned, or dried legumes.	grams/day
Whole grains	Average daily consumption of less than 140-160 g of whole grains from breakfast cereals, bread, rice, pasta, biscuits, muffins, tortillas, pancakes, and other sources.	grams/day
Nuts and seeds	Average daily consumption of less than 10-19 g of nuts and seeds.	grams/day
Milk	Average daily consumption of less than 360-500 g of milk including non-fat, low-fat, and full-fat milk, excluding plant derivatives.	grams/day
Red meat	Any intake of red meat including beef, pork, lamb, and goat but excluding poultry, fish, eggs, and all processed meats.	grams/day
Processed meat	Any intake of meat preserved by smoking, curing, salting, or addition of chemical preservatives.	grams/day
Sugar-sweetened beverages	Any intake of beverages with ≥50 kcal per 226.8-g serving, including carbonated beverages, sodas, energy drinks, and fruit drinks, but excluding 100% fruit and vegetable juices.	grams/day
Fiber	Average daily consumption of less than 21-22 g of fiber from all sources including fruits, vegetables, grains, legumes, and pulses.	grams/day
Calcium	Average daily consumption of less than 1.06-1.1 g of calcium from all sources, including milk, yogurt, and cheese.	grams/day
Seafood omega-3 fatty acids	Average daily consumption of less than 430-470 mg of eicosapentaenoic acid and docosahexaenoic acid.	milligrams/day
Polyunsaturated fatty acids	Average daily consumption of less than 7%-9% of total energy intake from polyunsaturated fatty acids.	total percentage of daily energy intake
Trans fatty acids	Any intake of trans fat from all sources, mainly partially hydrogenated vegetable oils and ruminant products.	total percentage of daily energy intake
Sodium	Average 24-hour urinary sodium excretion greater than 1-5 g.	grams/day

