Ultra-processed foods (optional)	Any intake of ultraprocessed foods, as defined by the Nova system as any food item in Nova category 4 (“ultraprocessed food”), in grams [20].	grams/day

^a^Based on the GBD (Global Burden of Diseases, Injuries, and Risk Factors Study) risk exposure definitions (Pages 217-218 in Supplementary Appendix 1 in the study by the the GBD 2019 Risk Factors Collaborators [19]).

^b^GBD: Global Burden of Diseases, Injuries, and Risk Factors Study.

^c^Analyses using continuous exposures are required by the GLAD Taskforce. The units listed here are recommended, however, these may be rescaled to more meaningful units in papers (eg, per 10 g) provided the original units are available to the project team.

**Table 2 table2:** Mental health definitions and recommended coding for the GLAD^a^ project^b^.

Mental disorder	Outcome definition	Diagnostic reference	Recommended coding^c^
Major depressive disorder	Involves the presence of at least one major depressive episode, which is the experience of either depressed mood or loss of interest/pleasure, for most of every day, for at least two weeks.	DSM-IV-TR^d^: 296.21–24; 296.31–34. ICD-10^e^: F32.0-9; F33.0-9.	0=no MDD^f^; 1= MDD
Anxiety disorders (any subtype)	Involves experiences of intense fear and distress, typically in combination with other physiological symptoms. Anxiety disorders will be modeled as a single cause for “any” anxiety disorder to avoid the double-counting of individuals meeting criteria for more than one anxiety disorder. Epidemiological estimates reporting an outcome for “any” or “total” anxiety disorders will be included if they reported on at least three anxiety disorders.	DSM-IV-TR: 300.0-300.3; 208.3; 309.21; 309.81. ICD-10: F40-42; F43.0; F43.1; F93.0-93.2; F93.8.	0=no anxiety disorder; 1=anxiety disorder

^a^GLAD: Global burden of disease Lifestyle And mental Disorders.

^b^The definitions and diagnostic references presented in this table are the current definitions used by the GBD (Page 4 in the Supplementary Appendix in the study by the GBD 2019 Mental Disorders Collaborators [1]). Since GLAD members may use alternative methods to ascertain disorder status, definitions or diagnostic references may vary slightly. For example, somatic forms of depression may be captured more by symptom scales, or studies using prescriptions may use Anatomical Therapeutic Chemical codes to determine incident depression and anxiety.

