### Future Directions: Meta-Analyses

Upon completion of the analysis phase of the GLAD project (phase 2), the GLAD project team and advisory group will lead a meta-analysis (phase 3). A separate protocol will be created for this phase of the GLAD project. Briefly, the GLAD project team will conduct a systematic literature review to identify any relevant studies not already participating in GLAD. After screening abstracts and full text, data will be extracted from all identified studies and studies participating in GLAD. A random effects meta-analysis will be performed to pool results from all eligible studies. We will perform a meta-regression to quantify how the risk can vary by demographic factors, and methodological biases [42]. Where studies have used different assessment methods for mental health outcomes, different tools to ascertain dietary intake, any slight deviations to definitions, or where studies use different analysis strategies, we will perform cross-walking or sensitivity analyses to ensure comparability [43]. Papers using methods that deviate substantially from the methods described in this paper will be excluded from the meta-analysis. The resulting meta-analysis will be reported according to the PRISMA (Preferred Reporting Items for Systematic Reviews and Meta-Analyses).

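### Each member study may replace the per-unit slope with its own nonlinear form, and no common form, contrast or retained linear estimate is required for pooling

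*Protocol article*

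**What the plan says.** The exposure scale is set in Table 1, footnote c: "Analyses using continuous exposures are required by the GLAD Taskforce". The same footnote lets papers change units: "these may be rescaled to more meaningful units in papers (eg, per 10 g) provided the original units are available to the project team". This covers linear rescaling only.

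The section Estimating Risk Ratios, Odds Ratios, and Hazards Ratios asks each study to check model assumptions and continues: "Should any model assumptions be violated, an alternate approach to analysis may be selected". Its example is that "the nonlinearity of continuous variables should be investigated, and transformations or nonlinear models fitted where necessary".

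Textbox 1, under Covariates and Confounders, makes three models mandatory (unadjusted, minimally adjusted, and energy-adjusted as a sensitivity model). These fix the covariates and leave the shape of the exposure open.

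Future Directions: Meta-Analyses plans a random effects meta-analysis under a separate protocol. It says that "where studies use different analysis strategies, we will perform cross-walking or sensitivity analyses to ensure comparability", and then: "Papers using methods that deviate substantially from the methods described in this paper will be excluded from the meta-analysis".

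**The concern.** The project exists to produce study-level estimates that can be pooled. For that, the exposure term must mean the same thing in every study. Here its form is decided study by study after the data have been examined, and the alternative may stand in place of the per-unit slope. One cohort could report a risk ratio per gram, another per doubling of intake, and a third a set of spline coefficients on its own knots.

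Three things follow:
- The coefficients are on different scales and cannot be averaged.
- Conversion to a common contrast needs outputs that the study-level phase does not ask for. The Results section has the pooling phase begin when the study-level phase is complete, so a later protocol would have to go back to each study.
- Where studies do stay linear, a nonlinear dose-response makes the slope depend on where the cohort's intakes lie. That would look like heterogeneity between countries.

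**Working it through.** The plan gives no figure on this point, so there is none to reproduce. The check has two parts.

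**1. What is fixed and what is open**

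| Item | Fixed? | Where |
|---|---|---|
| Continuous exposure | Yes | Table 1, footnote c |
| Units | Recommended; rescaling allowed | Table 1, footnote c |
| Covariates | Yes | Textbox 1 |
| Form of the exposure term | No, study by study | Estimating Risk Ratios section |
| Linear estimate kept beside an alternative | Not required | Estimating Risk Ratios section |
| Reference intake, knots, contrast | Not set | nowhere in the article |
| Covariances or predicted risk ratios | Not requested | nowhere in the article |

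**2. Illustration of size**

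Only the location of the kink relates to the documents: 325 g is the midpoint of the fruit range in Table 1 ("Average daily consumption of less than 310-340 g of fruit"). All other inputs are assumptions.

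*Slope under an all-linear analysis.* Assume risk = 0.10 × exp(b × min(x, 325)) with b = ln(0.75)/325. The true risk ratio (RR) per 100 g below the kink is exp(100b) = 0.915 (log −0.0885). Intake is gamma-distributed. A log-link Poisson model, linear in intake, is fitted to the expected risks without outcome noise.

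| Mean (SD), g/day | Share above 325 g | Fitted RR per 100 g | Fitted ÷ true log slope |
|---|---|---|---|
| 150 (110) | 8% | 0.931 | 0.0719/0.0885 = 81% |
| 250 (170) | 27% | 0.955 | 0.0461/0.0885 = 52% |
| 350 (210) | 47% | 0.972 | 0.0284/0.0885 = 32% |
| 450 (250) | 64% | 0.984 | 0.0163/0.0885 = 18% |

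All four cohorts share one dose-response curve.

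*Mixing of forms.* A second set of assumptions uses RR 1.30 for 0 g against 325 g, flat above, with gamma intake of shape 4. The true RR for 10 g against 325 g is exp(ln(1.30) × 315/325) = 1.29. The linear model implies (RR per 100 g)^(−3.15). The log model uses log(intake + 1).

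| Mean, g/day | Linear: RR per 100 g | Log: RR per doubling | 10 g vs 325 g, linear | 10 g vs 325 g, log |
|---|---|---|---|---|
| 150 | 0.927 | 0.932 | 1.27 | 1.41 |
| 300 | 0.964 | 0.924 | 1.12 | 1.48 |
| 450 | 0.986 | 0.947 | 1.05 | 1.30 |

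With the kink moved across 310 to 340 g, and the contrast taken as 10 g against the kink, the linear values run from 1.04 to 1.28 and the log values from 1.28 to 1.50. When all three cohorts use the same correctly shaped term (shortfall below 325 g), each returns 1.084 per 100 g shortfall.

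**The case against.** The strongest reply has four parts.

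**Pooling is provided for.** The meta-analysis section promises cross-walking or sensitivity analyses where analysis strategies differ, and defers detail to a separate protocol. A reader might infer that the estimates cannot be pooled at all. The documents do not support that, because fitted curves can be converted to a common contrast. What stands is that the inputs for conversion are not requested in the phase that generates them.

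**Exclusion is by method.** A reader might also infer that a study that finds curvature would be dropped because of its results. The rule reaches only methods that deviate substantially from those described, and a nonlinear fit made under the analysis section is itself a described method. What stands is that substantially has no criterion, so the status of such a fit is left to later judgement.

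**Table 1 does not give dose-response shapes.** Its entries are exposure definitions. The Introduction says that the Global Burden of Disease study does not yet have these estimates for common mental disorders. Eleven of its 15 exposures have a non-zero threshold (ten with a lower limit, and sodium with an upper one). Four are defined as any intake, for example "Any intake of red meat including beef, pork, lamb, and goat". Flattening at a threshold is therefore an assumption. This objection stands in full.

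**The attenuation figures argue for checking nonlinearity.** They do: the instruction to investigate curvature is sound. The gap is the absence of a common output once it is found. It is also tempting to say that small cohorts would miss the curvature and stay linear. The plan sets no significance test as a gate, so that is conjecture.

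**Conclusion.** The point holds as a gap in harmonization. The functional form is left to each study, the per-unit estimate may be replaced, and no common nonlinear form or contrast is fixed. This applies to every continuous exposure, including the four defined by any intake.

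The textual part rests on no assumption. The size does: the fall from 81% to 18% of the true log slope, and the spread of implied risk ratios from 1.05 to 1.48 around a true 1.29, depend on an assumed kink, a flat curve above it, assumed effect sizes and assumed intake distributions. They show what could happen and are not estimates for this project. The change should be made before member studies finish their analyses, because it is hard to recover the outputs afterwards.

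**What to change.** In Estimating Risk Ratios, Odds Ratios, and Hazards Ratios:
- Require every study to report the per-unit log-linear estimate for every exposure-outcome pair, whether or not linearity appears to hold.
- Beside it, require one centrally specified nonlinear output on the un-residualised intake scale: a restricted cubic spline with common absolute knots and a common reference intake. Studies report the coefficients with their covariance matrix, or predicted risk ratios with confidence intervals at set intakes.
- Set the knots centrally for each exposure. They need not sit at the Table 1 threshold. No such threshold exists for the four any-intake exposures, and the sodium range (1 to 5 g) is too wide to place one. Absolute knots also do not carry over to energy-adjusted residuals, hence the un-residualised scale.
- Allow study-specific transformations as additional analyses only.

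In Future Directions: Meta-Analyses, state that an alternative permitted by the analysis section is not a substantial deviation.

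The cost is one central table of knots and reference intakes, and one extra output per exposure-outcome pair: 15 exposures × 2 outcomes = 30 per study, or 32 with the optional ultraprocessed foods.
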